### Power

We powered our trial to detect a moderate effect size based on arm-differences of proportions of prolonged grief, due to the dearth of pilot data on mean differences. We considered an 18% arm difference in rates of prolonged grief symptoms, assuming 27% in the RIVER plus EUC arm and 45% in the EUC only arm. Since the RIVER peer grief support model has not yet been evaluated in those specifically bereaved by drug overdose deaths, we conservatively used estimates of proportions reported on rates of PGD among those bereaved by suicide [6]. We will have 80% power to detect a moderate effect size of a Cohen’s d of 0.4. We based this calculation on a two-tailed test of proportions for the null hypothesis of no difference in arms, and a significance level of 0.05. We are also adequately powered to perform repeated measures analysis to detect a group by time interaction term in a mixed model to address Aim 3. With our proposed follow-up sample size (*n* = 208), we have 90% power to detect a group by time interaction, expecting a Cohen’s d of 0.4 as before, and assuming adjustment of the baseline grief score, and a correlation of 50% between repeated measures.

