### Aim 3 procedures

We will recruit people who are bereaved by overdose from our three partnering MEOs for an RCT comparing the RIVER peer grief model plus EUC to EUC alone. Participants will complete assessments at baseline and 3-, 6-, and 12-month follow up. The inclusion and exclusion criteria for the RCT will be identical to Aim 2 unless advised otherwise by the advisory boards. We aim to recruit 320 people with a goal of 65% retention (208 people) at the 12-month follow-up.

We will also recruit the RIVER peer grief allies (up to 10) to complete a baseline and follow-up survey prior to and after the RCT. They will also be invited for a brief qualitative interview post-RCT to assess their experiences delivering peer grief support.

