### Data management and analysis plan

Aim 3 will test the effect of receiving the RIVER peer grief support model plus EUC compared to EUC alone by contrasting outcomes of grief and using regression-based modeling to leverage all time points while adjusting for the stratification variable. We will use Intent-to-Treat analyses. Hypotheses regarding the effectiveness of the RIVER peer grief support approach will be tested with a repeated measures mixed-effects linear model, with experimental group, time (4 assessment time points), and their interaction as fixed effects. Inclusion of the interaction term will allow for examination of the difference in response trajectories between intervention arms. We will also include the stratification variable as a covariate in the model. For missing data, we will proceed with likelihood-based mixed-effects models, which are valid under the Missing at Random (MAR) assumption. For non-ignorable missingness, we will add sensitivity analyses. Qualitative interview data with peer grief allies will also be used to contextualize quantitative results. For example, if allies share that support was more or less challenging for certain groups, we may explore potential moderators of the treatment effect.

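### The 90% power for the group-by-time interaction assumes a baseline adjustment that the stated analysis model does not make

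*Protocol article*

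**What the plan says.** The Power section first sizes the trial on a two-tailed comparison of proportions. It then adds that, at the follow-up sample size of 208, "we have 90% power to detect a group by time interaction". The effect size is the same d of 0.4 that the section uses earlier. Two further conditions are attached to the calculation: "assuming adjustment of the baseline grief score, and a correlation of 50% between repeated measures".

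The section on data management and analysis defines the model that tests effectiveness. It is a repeated-measures linear mixed model "with experimental group, time (4 assessment time points), and their interaction as fixed effects". The assessments are at baseline, 3, 6 and 12 months, so the four time points include baseline as an outcome. On covariates it says: "We will also include the stratification variable as a covariate in the model". It names no baseline grief covariate and states no constraint that the arms share a baseline mean. The analysis is intention-to-treat and likelihood-based, under missing at random.

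On numbers, the Aim 3 procedures say "We aim to recruit 320 people". The target for keeping them in the study is stated there as a "goal of 65% retention (208 people) at the 12-month follow-up".

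**The concern.** The two sections treat baseline differently. The power sentence takes credit for the precision gained by adjusting for baseline. The model gives that precision up: with a free group effect and baseline as an outcome row, the 12-month group-by-time term is, in balanced data, a difference in change from baseline. At a correlation of 0.5 a change score is no more precise than the follow-up score alone.

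The power sentence also does not say which interaction test is meant (the 12-month contrast, a slope, or the overall 3-df test) or how the effect of 0.4 is spread over the visits. The 90% therefore cannot be tied to a test that the plan specifies. What is at stake is a power claim for the main effectiveness model that the model, as written, does not support, and precision that could be had at no cost.

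**Working it through.** **Inputs from the protocol article.** 208 at 12 months, taken as 104 per arm (allocation is approximately equal); d = 0.4; correlation r = 0.5; alpha 0.05.

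**Assumptions.** Two-sided testing, which is stated for the proportions test and carried over here; outcome SD of 1; the same correlation between all pairs of visits (compound symmetry). Power is Φ(d/SE − 1.96).

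**1. Reproducing the 90%.** Baseline-adjusted comparison at one follow-up:
- residual variance = 1 − 0.5² = 0.75
- SE = √(2 × 0.75/104) = 0.1201
- d/SE = 3.331, so power = Φ(1.371) = 91.5% (noncentral t: 91.2%).

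Other two-sided readings are further away or drop the stated adjustment: unadjusted single follow-up 82.2%; mean of three follow-ups 94.2%; baseline-adjusted mean of three follow-ups 99.4%. A one-sided test of the change contrast would give 89.2%, but the only sidedness the section states is two-tailed, and that reading uses no baseline adjustment.

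**2. The 12-month interaction contrast in the stated model, same inputs.**
- variance of change = 2(1 − 0.5) = 1
- SE = √(2 × 1/104) = 0.1387
- d/SE = 2.884, so power = Φ(0.924) = 82.2% (noncentral t: 81.9%).

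For 90% on this contrast, n per arm = 2(1.960 + 1.282)²/0.4² ≈ 131.4, so 132 per arm or 264 in all, against 208.

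**3. The overall 3-df interaction test.** Noncentrality = (104/2) × Σ(dⱼ − mean d)²/(1 − 0.5), noncentral chi-square. The patterns are assumptions, since the article gives none. The last column lets all 320 enter the likelihood analysis, with assumed counts of 160/142/123/104 per arm at the four visits; the article gives only the first and last.

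| Effect at 0/3/6/12 months | Σ(dⱼ − mean d)² | Noncentrality | Power, 208 completers | Power, all 320 |
|---|---|---|---|---|
| 0/0.1/0.2/0.4 | 0.0875 | 9.10 | 72% | 76% |
| even rise by visit to 0.4 | 0.0889 | 9.24 | 72% | 79% |
| 0/0.3/0.4/0.4 | 0.1075 | 11.18 | 81% | 91% |
| 0/0.2/0.4/0.4 | 0.1100 | 11.44 | 82% | 90% |
| 0/0.4/0.4/0.4 | 0.1200 | 12.48 | 86% | 95% |
| 0/0/0/0.4 | 0.1200 | 12.48 | 86% | 86% |
| 0/0/0.4/0.4 | 0.1600 | 16.64 | 94% | 97% |

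**4. The 12-month contrast with all 320.** If every dropout occurs before month 3, the other 56 per arm contribute baseline only:
- variance per arm = 0.75/104 + 0.25/160 = 0.008774
- SE = √(2 × 0.008774) = 0.1325
- d/SE = 3.020, so power = Φ(1.060) = 85.5%.

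With the gradual dropout of step 3 it is 86.6%.

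**5. Common baseline mean.** If the arms share one baseline mean, the 12-month arm contrast has variance 2 × 0.75/104, as in step 1. Power is 91.5% on 208 completers, with baseline still an outcome row.

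**The case against.** Four arguments can be made for the text as it stands.

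- **The planned analysis uses all 320 by likelihood, so 82% understates it.** This stands. The 12-month contrast then has about 86–87%, and several patterns reach 90% or more on the 3-df test. But the power sentence is itself written for n = 208, and the 12-month contrast stays below 90% under both dropout assumptions tried.
- **A mixed model adjusts for baseline implicitly.** It does so only if the arms are held to a common baseline mean. The article lists group as a fixed effect beside its interaction with time and states no such constraint.
- **The sample size does not rest on this figure.** This stands. The trial was sized on the test of proportions, and the interaction statement is supplementary. A reader might infer that the sample size is invalid; the documents do not support that.
- **An article condenses, and a fuller plan may name the contrast.** That excuses missing detail. It does not excuse two printed statements that disagree about baseline.

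A reader might also infer that the planned model has 82% power or less for most effect patterns. The documents fix neither the test nor the pattern, and the results on completers run up to 94%, so that reading does not hold.

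**Conclusion.** The power statement and the analysis model do not match. The 90% is closest to a baseline-adjusted single follow-up contrast (about 91%), which the stated model does not estimate. Under the stated inputs, that model gives about 82% for the 12-month interaction contrast on 208 completers, about 86–87% with all 320, and about 72% to 94% on the 3-df test on completers.

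These figures rest on compound symmetry at 0.5, two-sided testing and equal arms. The 320-based figures also rest on assumed dropout timing, and the 3-df range on assumed effect patterns. It is therefore tempting but unsafe to put 82% in place of 90%: no single figure follows until the tested contrast is named. Severity is moderate, because the sample size was justified separately.

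**What to change.** **Preferred.** Keep the four time points but constrain the arms to a common baseline mean: time, arm-by-post-baseline-time terms, the stratum, and no arm effect at baseline. Name the 12-month arm contrast as the tested quantity. Restate the power for that contrast: about 91% at n = 208 with d = 0.4 and r = 0.5.

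**If the current model stays.** Name the interaction contrast to be tested, remove the baseline-adjustment assumption from the power sentence, and restate the power for that contrast. For the 12-month contrast this is about 82% at n = 208, or about 86–87% using all 320 with the dropout assumption written down.

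The cost is rewording the model and power paragraphs. No further participants or data are needed. The change should be made before outcome data are seen.

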### Discussion

Our nation is experiencing historic rates of drug overdose deaths that have left behind millions of bereaved families. People who are bereaved by overdose experience a “special grief” that compounds suffering and help-seeking. Overdose bereavement is an unfortunate and common reality for many Americans, and the ripple effect of overdose deaths may increase risk for overdose morbidity and mortality among the bereaved. No evidence-based interventions exist to support this population and the science must catch up. Peer grief support interventions hold promise and may be especially crucial for this population given the increased stigma, isolation, and risks this population faces. This study seeks not only to understand whether a peer support model aids those grieving an overdose death, but also to explore the feasibility and acceptability of proactively engaging grievers through MEOs. In doing so, we aim to reach out to grievers who may not otherwise seek care. If our study is successful, our practice-research partnership and engagement of advisory board members will propel the translation of research to practice and address the large toll the overdose crisis takes on this overlooked population.

## Data Availability

No datasets were generated or analysed during the current study.
